### Description of the Study Intervention

Every 2 weeks, the intervention group will receive a URL via WhatsApp linking to the website displaying user ratings of health care facilities that provide pediatric care. Although the survey is short, we were concerned about potential survey fatigue and, therefore, limited study participation to 12 weeks (6 survey rounds).

The website will consist of 3 unique pages, as shown in Figures 1-3, and will be accessible to anyone with an internet connection. All text will default to Lao, the official language of Lao PDR, while an English version will also be available for demonstration purposes. The logo of the Lao Tropical and Public Health Institute will be displayed at the top of the facility ratings website.

The website will consist of 3 unique pages: the home page, a listing of health care facilities (second page), and a detailed review of a single facility covering multiple quality components (third page). Figure 1 shows the home page. Figure 2 displays the list of health care facilities, with those having the highest average overall rating shown at the top. Only facilities with at least three reviews will be listed, while those with fewer reviews will be hidden. Clicking on any health facility will display reviews and average ratings for multiple quality components of that facility—provider skill, respectfulness of the provider, cost, cleanliness, equipment, and waiting time—along with comments left by recent users (Figure 3). The website’s design will remain fixed for the duration of the study; however, the ratings will be updated as participants submit new entries.

Health facility reviews will be generated based on biweekly reports of recent visits by all participants. Participants will receive a WhatsApp message asking whether they have visited a health care facility for their child in the past 2 weeks. Those who respond “yes” will receive a link to complete a short survey to review or rate their experience. The overall quality rating, which determines the order of facilities on the website’s second page (see Figure 2), is calculated based on participants’ responses to the question: “How would you rate the overall quality of the health facility?” Participants are asked to select 1 of the following response options: “excellent,” “very good,” “good,” “fair,” or “poor.” The average rating is calculated using numerical values assigned to these responses, with scores ranging from 5 (excellent) to 1 (poor). Golden stars visually represent the overall average quality rating. To further assist participants in exploring health facilities, hyperlinks to each facility’s address and phone number are provided, along with their opening hours.

Figure 3 shows the average ratings across multiple quality domains for a selected health facility, along with comments on participants’ experiences. Participants can access this information by selecting the facility’s name on the website’s second page (Figure 2).

**Figure 3 figure3:**
[figure not shown]
Third page of the website (intervention).

### Auditing

No audits are planned. The principal investigator will be in Lao PDR during enrollment, baseline, and endline surveys. While in Lao PDR, he will monitor the progress of enrollment and survey responses daily and will remotely oversee the progress of mobile phone surveys every week. His review will include checking the progress and accuracy of enrollment logs, versions of enrollment logs, and the completeness of baseline and endline survey responses. Additionally, he will supervise the weekly web-based surveys that collect quality ratings of health facilities and ensure the functionality of the website.

### Interim Analysis and Stopping Guidelines

Interim analyses are not planned for this study. Enrollment will stop once 660 participants have been recruited. Participants may withdraw from the study at any time. If the study team is uncertain whether a participant intends to withdraw, they may attempt to contact her up to 3 times at different times of the day. If she remains unreachable, the study team will conclude her participation.

The study team may discontinue a survey with an individual participant if she is not reachable after 3 attempts or if she has not responded to consecutive mobile survey questions. The project sponsor may terminate the study prematurely under certain circumstances, including ethical concerns, insufficient participant recruitment, or an inability to continue data collection due to public health emergencies.

### Study Design

This study is an unblinded randomized controlled experiment with rolling enrollment. Participants’ preferred facility for nonurgent care will be recorded during the baseline survey, immediately following enrollment. A detailed overview of the methodology and timing of the intervention is shown in Figure 4.

**Figure 4 figure4:**
[figure not shown]
CONSORT (Consolidated Standards of Reporting Trials) study flow diagram.

### Sample Size Determination

The required sample size was calculated based on the proportion of mothers who changed providers for nonurgent care in a 6-week pilot study involving 58 participants. In the pilot, all participants received the intervention—a web page of facility ratings—once or twice, depending on when the endline survey was scheduled. A conservative sample size was calculated to detect a 12-percentage-point change in the outcome with 80% power and α=.05; 330 participants per group would be required. Assuming 10% attrition, the total required sample size was set at 660 participants.

### Randomization

Participants will be randomized using the ODK package installed on tablets at enrollment. A simple random number generated by ODK will assign participants to the treatment or control group with equal probability.

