**Methods:**

Mothers with at least one child under 2 years of age who are already enrolled in the Vientiane Multigenerational Birth Cohort (VITERBI) will be invited to participate during in-person visits by the research staff. Participants will be randomly assigned in equal numbers to the control and intervention groups. The intervention group will receive a URL with facility ratings for pediatric health care services every 2 weeks via WhatsApp; the control group will not receive any messages. WhatsApp will also be used to administer biweekly surveys to both groups to assess the quality of care received in the past 2 weeks. The web page shared with the intervention group will display results from these surveys and from the pilot study. Research staff will conduct baseline and endline surveys with all participants during in-person visits, 3 months apart.

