## Methods

### Participants and Randomization

This study consists of a randomized controlled experiment involving 660 mothers with children under 2 years of age from an ongoing VITERBI study, which includes the local population of young mothers in 4 districts of Vientiane Capital. Mothers with at least one child under 2 years old, already enrolled in the VITERBI study and living in 1 of 2 urban districts (Sikhottabong or Chanthabouly), will be invited to participate in the study during in-person visits by the research staff. We will use rolling enrollment while ensuring that each participant is enrolled in the study for a maximum of 3 months. Participants will be randomly assigned to 1 of 2 groups: (1) a control group that will not receive any information about providers, and (2) an intervention group that will receive biweekly updates on quality ratings based on reviews collected from mothers of young children in the study areas. The unit of randomization will be the individual participant. A simple random number draw, generated by the Open Data Kit (ODK) package installed on the tablets, will be used to assign participants to treatment or control with equal probability.

Research staff will administer baseline (see Multimedia Appendix 1) and endline (see Multimedia Appendix 2) surveys to all participants during in-person visits held 3 months apart. Responses to these surveys will be used to measure the study’s primary outcome: the proportion of mothers who changed their preferred health care facility for nonurgent child care services between the 2 surveys. This outcome assesses whether information about health care providers can influence users to seek alternative sources of care. For a completed CONSORT-EHEALTH (Consolidated Standards of Reporting Trials of Electronic and Mobile Health Applications and Online Telehealth) checklist, see Multimedia Appendix 3.

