### Study Procedures

Research staff, with support from the respective village offices, will recruit participants during in-person visits. At the first meeting, before enrollment and the baseline survey, research staff will explain the study and obtain informed consent. The informed consent will cover key information, including the study’s objectives, duration, level of participant involvement, and the assurance that participation is entirely voluntary. Tablets equipped with ODK will be used to record responses from enrolled participants during the baseline and endline surveys. All participants will receive a small gift in appreciation of their participation, in keeping with customary practice in Lao PDR.

After completing the baseline survey, research staff will assist all enrolled participants in connecting with the study’s WhatsApp number and will demonstrate how to submit biweekly user ratings of facilities. In addition, staff will encourage participants in the intervention group to use the website, as needed, to access information on pediatric health care facilities and view user ratings submitted by their peers. Research staff will demonstrate the 3 main pages of the website, show participants how to navigate between them, and answer any questions they may have. The study coordinator will record enrolled participants weekly, along with their group assignment (intervention or control), and will schedule dates for each participant to receive biweekly surveys, the intervention URL (for those in the intervention group), and the endline interview.

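### As written, the random draw precedes the baseline survey, so the baseline half of the primary change outcome is collected after allocation with no stated concealment from the interviewer

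*Protocol article*

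**What the plan says.** All references are to the protocol article.

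- **Time of the draw** (Randomization): "Participants will be randomized using the ODK package installed on tablets at enrollment". It is a simple random number with equal probability for each arm.
- **Time of the baseline answer** (Study Design): "Participants’ preferred facility for nonurgent care will be recorded during the baseline survey, immediately following enrollment".
- **Sequence of the visit** (Study Procedures): "At the first meeting, before enrollment and the baseline survey, research staff will explain the study and obtain informed consent". The same section adds: "Tablets equipped with ODK will be used to record responses from enrolled participants during the baseline and endline surveys".
- **Primary outcome** (Outcomes): a binary indicator of whether the facility named for a mild fever with cough differs between baseline and endline. Secondary outcomes 3 (most recently visited facility) and 5 (preferred facility for urgent care) are also changes from baseline to endline.
- **Blinding** (Study Design, Blinding, Limitations): the trial is open-label. The one masking measure is that the analyst is blinded during the endline assessments. The staff member who messages the intervention group is kept away from endline surveys and other administrative assessment work; the baseline interview is not named.
- **Arm sizes**: the Abstract states "Participants will be randomly assigned in equal numbers to the control and intervention groups", and Outcomes plans 330 per arm.

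**The concern.** In most trials a baseline measure taken after allocation weakens only a covariate. Here it is one of the two answers that define the primary outcome, and it is a stated preference in a hypothetical scenario, given face to face. If the interviewer or the mother knows the arm when the question is put, probing, recording or the answer itself could differ by arm. A mother could also stop before naming a facility once she knows her arm. She would then have no primary outcome, and Statistical Analysis excludes participants with missing outcomes without imputing them. Either route could produce a difference in apparent switching that does not come from the ratings website.

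**Working it through.** **1. Order of events, from the text.**

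| Step | Section | What it fixes |
|---|---|---|
| Consent | Study Procedures | before enrolment and before the baseline survey |
| Random draw | Randomization | at enrolment, on the tablet |
| Baseline survey | Study Design | straight after enrolment |
| Respondents to baseline | Study Procedures | women already enrolled |
| WhatsApp set-up for all; website demonstration for the intervention group | Study Procedures | after the baseline survey |

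Read together, the order is consent, enrolment with the draw, baseline answers, then arm-specific steps. No section says that the answers are saved before the draw, or that its result is hidden until they are.

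**2. Safeguards.** Analyst blinding applies at endline. The separation of staff roles names endline and other administrative assessment work. Neither is stated to cover the baseline interview, which Participants and Randomization assigns to research staff ("Research staff will administer baseline"). Study Procedures gives the website demonstration to research staff as well.

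**3. Illustration of what a bias would do.** The documents give no figure for such a bias, so there is nothing to reproduce; the shift *b* is an assumption. Inputs: *n* = 300 per arm (600 endline surveys expected, Outcomes); switching rate *p* = 0.45 (pilot, 26/58); and, as an assumed lower rate, *p* = 0.33. There is no true effect, and one arm records *q* = *p* + *b*.

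- p̄ = (p + q)/2
- SE₀ = √[2p̄(1 − p̄)/n]
- SE₁ = √[(p(1 − p) + q(1 − q))/n]
- Rejection probability = 1 − Φ[(1.96·SE₀ − b)/SE₁] + Φ[(−1.96·SE₀ − b)/SE₁]

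For *p* = 0.45 and *b* = 0.03: p̄ = 0.465, SE₀ = 0.0407, SE₁ = 0.0407. The two arguments are 1.224 and −2.698, giving 0.1105 + 0.0035 = 0.114.

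| Assumed shift in one arm | False-positive rate, p = 0.45 | False-positive rate, p = 0.33 |
|---|---|---|
| 1 point | 5.7% | 5.8% |
| 2 points | 7.8% | 8.1% |
| 3 points | 11.4% | 12.1% |
| 5 points | 23.2% | 24.8% |
| 8 points | 50% | 53% |

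**4. Equal numbers under a simple draw.** With 660 independent draws at probability 0.5, the number in one arm is Binomial(660, 0.5), with SD √(660 × 0.25) = 12.85. The chance of exactly 330/330 is 3.1%, and the 95% range for one arm is 305 to 355. At 305/355 the effective size per arm is 2 × 305 × 355/660 = 328.1, against 330, a loss of 0.6%.

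**The case against.** The strongest reply is that enrolment, draw and survey all belong to one in-person visit, so the two timing phrases may be loose. The only step-by-step account, in Study Procedures, puts every arm-specific action after the survey, which fits a draw at the end of the ODK form. Study Design refers the timing to Figure 4, which is not available here. The mother has seen no ratings when she answers, the interviewer cannot know her endline answer, and no direction of bias is evident.

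Much of this stands. It limits how far the point can be taken:

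- A reader might infer that staff knew the arm while asking the baseline question. The documents do not say so; it is an inference from the stated order and the open-label design.
- A reader might infer that the primary outcome is biased beyond repair. The documents show a route for bias, not that bias occurred or how large it is.
- A reader might infer that the baseline covariates are unsafe for adjustment. Age, wealth, education and ethnicity are unlikely to change because the arm became known minutes earlier. Self-reported parental health literacy is the only listed covariate for which this is plausible, and adjustment is a secondary analysis.
- A reader might infer that permuted blocks are required. The loss from a simple draw is under 1% even at the edge of the 95% range, and in an open-label trial blocks make later assignments easier to predict.

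The reply does not remove the core. The protocol does fix the timing of allocation relative to a component of the primary outcome, and as worded it puts allocation first.

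**Conclusion.** The point holds as a risk created by the stated sequence. The baseline half of the primary outcome, and of secondary outcomes 3 and 5, is collected after allocation in an open-label trial, and no stated measure conceals the arm from the baseline interviewer. This rests on taking the enrolment wording in Randomization and Study Design at face value. The size of any bias is unknown: the rates of about 11–12% for a 3-point shift and 23–25% for a 5-point shift describe assumed shifts only. If the draw already sits at the end of the baseline form, the defect is one of wording.

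The equal-numbers wording is a separate, minor inconsistency with negligible effect on power.

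**What to change.** 1. Amend Randomization and Study Design so that the ODK draw is made and revealed only after all baseline answers are saved and locked, and bring Study Procedures into line. If this is already the practice, correct the wording to say so. Cost: the position of one field in the ODK form and a sentence or two of text.
2. The trial is under way, so reordering the form helps only mothers still to be enrolled. For those already enrolled, confirm from the ODK form which order was used and report it with the results. Cost: a check of the form.
3. In the Abstract and Outcomes, describe equal allocation and 330 per arm as expected numbers under a simple draw. No change to the randomisation method is needed.

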### Blinding

This will be an “open-label” trial; however, the analyst will be blinded during the endline assessments.

### Adverse Events

We do not anticipate any adverse events resulting from this study. Participants will receive, via WhatsApp, a URL linking to the website containing quality ratings of health care facilities for children in Vientiane Capital.

### Unexpected Events

We have developed study procedures and a detailed calendar to ensure a shared understanding of key activities and their timelines. These measures are also designed to minimize the impact of unexpected events, such as staff changes. A journal will be maintained to track critical events, including website downtime.

### Equipment

We do not anticipate the need for additional equipment. Participants will use their own mobile phones to communicate with the research team.

### Attrition

We attempted to minimize loss to follow-up by excluding participants who permanently or temporarily moved away from the 2 study districts and by monitoring participant engagement throughout the study period. The study coordinator called participants who did not respond to the biweekly surveys to encourage participation and resolve any issues they may have been experiencing with accessing the data.

### Data Management

Survey data will be recorded using unique identifiers for each participant. An enrollment log will be maintained to link these codes with participants’ phone numbers and will be used solely for study administration. Responses to the baseline, endline, and mobile-based surveys will be stored electronically using only the individual codes, without any phone numbers.

AA and a research coordinator will maintain the enrollment logs electronically on a password-protected, secure Swiss TPH server that will be regularly backed up. The enrollment log will be saved using the following format to ensure traceability of any changes: LaosMR_enrol_v1.0_DD.MM.YYYY. The research team (AA, GF, and [name]) will have access to password-protected survey responses from the baseline, endline, and mobile phone surveys.

Data collected during the biweekly surveys will be stored on a password-protected cloud server, accessible only to the research team (AA, GF, and [name]). Hard copies containing participant information will be kept in a locked filing cabinet in the project office at the Lao Tropical and Public Health Institute. These files will be accessible only to the local study coordinator and enumerators responsible for conducting the baseline and endline surveys.

We will use WhatsApp for 2 main purposes: (1) to ask all participants whether they have visited a health care facility for their children in the past 2 weeks and, if they respond affirmatively, to send them a link to an online survey to rate the quality of care they received; and (2) to provide the intervention group with a URL link to the website displaying user ratings of health facilities for pediatric care. The local study coordinator will communicate with participants using a dedicated tablet and a unique WhatsApp account, used exclusively for the study. The tablet will be password-protected and accessible only to the local study coordinator. Messages exchanged between participants and the study coordinator on WhatsApp are secured with end-to-end encryption [17]. At the conclusion of the study, all contacts will be deleted, and the WhatsApp account will be disabled.

### Outcomes

Trial outcomes will be measured through the in-person endline survey. For the primary analysis, we will assess the proportion of mothers who changed their preferred health care facility for nonurgent child care services between the baseline and endline surveys. The null hypothesis is that there is no difference between the control and intervention groups. The alternative hypothesis is that there is a difference between the 2 groups. This hypothesis aligns with our study aims, as it examines whether the use of provider facility ratings influences caregivers to seek alternative sources of health care for their children. Our primary analysis is cross sectional; for the panel analysis using the care-seeking panel, observations will be clustered at the household level.

Nonurgent care is defined as a child presenting with a mild fever of 38°C accompanied by a cough. During the baseline and endline surveys, participants will be asked to specify their preferred location for child care using the following question: “If your child is sick tomorrow with a mild fever of 38°C Celsius and cough, which hospital, clinic, or health center would you take your child to?” The primary outcome will be a binary indicator reflecting whether participants changed their preferred location between baseline and endline.

We used the proportion of mothers who changed providers (n=26, 45%) for nonurgent care in a 6-week pilot study involving 58 participants. All participants in the pilot received the intervention—a web page of facility ratings. Eligible women will be randomly selected from the ongoing VITERBI study for enrollment, and recruitment will continue until we reach 660 participants, with 330 in each intervention arm, assuming 10% attrition. Enrolling 300 participants per intervention arm provides 90% power, with a 2-sided α of .05, to detect a 12-percentage-point change in health facility choice, assuming 80% follow-up. We will collect and analyze baseline and endline survey data from mothers enrolled in the study. We anticipate completing 600 endline surveys and analyzing this sample.

Additionally, we plan to measure 6 secondary outcomes to explore further effects of the intervention. These relate to caregivers’ actual health care use over the past 3 months, including satisfaction with care received, frequency of health care service use, and changes in the facility used for their most recent visit. Additionally, the secondary measures capture whether caregivers selected health facilities based on online or digital information, whether they changed their preferred provider for urgent care, and their confidence in identifying the best facility for their children’s care. The secondary measures are presented in Textbox 1.

Secondary measures.
**1. Proportion of mothers satisfied with health care for their children during their most recent visit (time frame: 3 months)**
This secondary outcome measure captures mothers’ satisfaction with the health care facility visited most recently for care of their child under age 2 years. This measure will be available only for mothers who sought care for their child during the study period. It will be a binary variable, with satisfaction defined as responding “excellent” or “very good” (as opposed to “good,” “fair,” or “poor”) to the question: “How would you rate the overall quality of care you received?” referring to the most recent visit for their child under age 2 years within the past 3 months.

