### Study Preparation Procedures

#### Overview

There were 3 preparatory phases leading up to the pilot. Phase 1 involved a preliminary survey of smartphone ownership and use among 36 randomly selected participants in the VITERBI study. In phase 2, we conducted cognitive interviews with 5 women to ensure the understandability of the baseline and endline questionnaires, and we tested both the understandability and usability of the website design prototypes. In phase 3, we conducted a pilot study with 68 participants to test the study procedures. The final phase involved conducting the main study.

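### The two sample-size statements conflict on power, number per arm and loss to follow-up, and the 90% power claim does not reproduce: 300 enrolled per arm at 80% follow-up gives about 75–77%

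*Protocol article*

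**What the plan says.** Sample Size Determination states the target as follows: "A conservative sample size was calculated to detect a 12-percentage-point change in the outcome with 80% power and α=.05". It continues: "330 participants per group would be required. Assuming 10% attrition, the total required sample size was set at 660 participants".

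Outcomes gives the pilot switching rate (26 of 58, 45%), notes that every pilot participant received the intervention, and sets recruitment at 660, or 330 per arm with 10% attrition. The next sentence reads "Enrolling 300 participants per intervention arm provides 90% power, with a 2-sided α of .05, to detect a 12-percentage-point change" in facility choice, on the assumption of 80% follow-up. The section then adds: "We anticipate completing 600 endline surveys and analyzing this sample".

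The pilot size also varies. The Overview under Study Preparation Procedures says "we conducted a pilot study with 68 participants to test the study procedures", while Sample Size Determination and Outcomes both describe 58 participants.

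**The concern.** One effect size, one alpha and one pilot rate carry two powers (80% and 90%), two enrolments per arm (330 and 300) and two losses (10% and 20%). The second account has fewer women enrolled and more of them lost, yet claims more power. Under common inputs that is impossible, so at least one account is wrong. Neither states a control-arm rate that might reconcile them.

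The stated power tells a reader how far a null primary result argues against a true 12-point effect. A claim of 90% puts the risk of missing such an effect at 10%. If the design does not deliver that, a null result will be read as stronger evidence of no effect than it is.

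**Working it through.** **Inputs from the documents**
- Difference: 12 percentage points (both sections).
- Alpha: .05 in both sections; Outcomes specifies "with a 2-sided α of .05".
- Planning rate: 26/58 = 44.8%, given as 45% (Outcomes).
- Allocation: equal probability (Randomization).
- Enrolment and loss: 330 per arm with 10% loss (both sections); 300 per arm with 80% follow-up (Outcomes).

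**Assumption.** No control rate is given. Since all pilot participants received the intervention, 45% is most naturally the intervention-arm rate, with 33% in controls. The alternative, 45% v 57%, is shown beside it.

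**Formula** (two proportions, pooled variance under the null, n analysed per arm, p̄ the mean of the two rates):

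Power = Φ{ [0.12·√n − 1.96·√(2p̄(1−p̄))] / √(p1(1−p1) + p2(1−p2)) }

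**The 90% sentence first.** 300 × 0.80 = 240 analysed per arm, and 0.12·√240 = 1.859.
- 45% v 33%: p̄ = 0.39; 1.96·√0.4758 = 1.352; √0.4686 = 0.6845; z = (1.859 − 1.352)/0.6845 = 0.741; power 77.1%.
- 45% v 57%: p̄ = 0.51; 1.96·√0.4998 = 1.386; √0.4926 = 0.7019; z = (1.859 − 1.386)/0.7019 = 0.674; power 75.0%.

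The stated 90% is not reproduced. Unpooled variance gives 77.5% / 75.5%, and a continuity correction gives 74.1% / 72.0%.

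**Other readings of the numbers**

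| Analysed per arm | Source | 45% v 33% | 45% v 57% |
|---|---|---|---|
| 240 | 300 × 0.8 | 77.1% | 75.0% |
| 264 | 330 × 0.8 | 80.9% | 78.9% |
| 297 | 330 × 0.9 | 85.2% | 83.5% |
| 300 | 600 endline surveys | 85.6% | 83.8% |
| 330 | 660 with no loss | 88.7% | 87.1% |

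No row reaches 90%, including the one with no loss at all.

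**Numbers needed**, solving the same formula for n:
- 80% power: 259 (45% v 33%) or 272 (45% v 57%) analysed per arm.
- 90% power: 346 or 363 analysed per arm, more than the 330 enrolled.

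**Could other inputs give 90%?**
- With 240 per arm and 12 points, power reaches 90% only well away from the pilot rate: at about 15% v 27%, or in the mirror case of about 73% v 85%. The documents support neither pair.
- A one-sided .05 test with 300 analysed gives 91.6% / 90.4%, but Outcomes says two-sided and assumes 80% follow-up. One-sided with 240 gives 85.5% / 83.9%. Whether the 90% arose in this way is not stated.

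**The case against.** The strongest reply is that the trial as it will run is adequately powered. Enrolment is fixed at 660. At 10% attrition that gives about 84–85% power, above the 80% target in Sample Size Determination; at 20% loss it gives about 79–81%. The 75–77% describes 300 enrolled per arm, which nobody plans. All of this stands. It limits the consequence, but it does not rescue the 90% sentence.

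Several stronger criticisms are tempting and are not supported:

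- **The trial carries a 25% risk of missing a 12-point effect.** That figure belongs only to the 300-per-arm sentence. For 330 per arm the risk is about 15–17% at 10% loss and 19–21% at 20% loss.
- **330 cannot be right for 80% power.** As an enrolment figure it can. At 80% follow-up it leaves 264, with 80.9% / 78.9% power. With a continuity correction, 45% v 57% needs 288 analysed, or 288/0.9 = 320 enrolled at 10% loss. The section also calls its size conservative. The fault lies in calling 330 required and then adding attrition.
- **Adding 10% attrition to 330 means enrolling 734.** Outcomes gives 330 per arm with 10% attrition already assumed, so 330 is the inflated number.
- **660 less 10% is 594, not 600.** This is rounding in an anticipated figure; power at 297 and at 300 differs by less than half a point.
- **The pilot lost 10 of 68 (14.7%), so at least 15% loss should be planned.** The documents do not say that 58 are the completers of 68. Even if they are, the exact 95% interval of about 7% to 25% includes 10%. Only the mismatch itself can be raised.

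**Conclusion.** The point holds for the two written statements. They are incompatible on power, number per arm and loss, and the 90% figure is not delivered. On its own terms the 90% sentence yields about 77% (45% v 33%) or 75% (45% v 57%). On the more generous reading of 300 analysed per arm it yields about 84–86%.

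This rests on the 45% pilot rate being the planning rate for one arm, a two-sided .05 test and a comparison of two independent proportions. A control rate far from the pilot figure would change the numbers, but none is stated. A reader might conclude that the trial is underpowered or needs more women; its own figures for 660 enrolled do not support that. What needs correcting is the stated power and its derivation.

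**What to change.** Delete the 90% power sentence in Outcomes and use one statement in both sections, along these lines:

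*330 women will be randomised per arm (660 in total), a number that already allows for attrition. The pilot switching rate of 45%, observed with all participants receiving the intervention, is taken as the intervention-arm rate; the assumed control rate is 33%. For this 12-percentage-point difference at two-sided alpha .05, 10% attrition (297 analysed per arm) gives about 85% power and 20% attrition (264 per arm) about 81%. If the rates were instead 45% and 57%, power would be about 83% and 79%.*

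The 33% is an example that follows from 45% less 12 points. The investigators should state the control rate they actually assumed.

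Also state whether the pilot had 68 or 58 participants and, if both figures are right, what each counts.

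The change is wording only: no extra enrolment and no change to conduct or analysis. The cost is a published power below 90%.
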